#### **3.5.2 Exclusion criteria**

Exclusion criteria for the children:

- Serious chronic illnesses and diseases that may interfere with study outcomes
- Diagnosed ADHD or other psychiatric illness
- Intake of medication that may affect study outcomes
- Concomitant participation in other studies involving dietary supplements or blood sampling
- Living in a household with another participating child

#### **3.5.3 Procedure for exclusion and withdrawal**

A participant can be excluded from the study if the clinically responsible physician finds it advisable due to medical reasons. A participant can also be excluded for ethical reasons e.g. if the project staff and/or clinically responsible physician judges that the child does not want to continue his/her participation in the study, which will always be respected. Finally, a participant can be excluded if non-compliance with the procedures described in the information material is clearly demonstrated. Reasons for exclusion will be recorded and parents will be informed about the decision.

Parents will be informed that they can withdraw their child from participation at any time without giving a reason. At withdrawal we will ask the parents if they will tell us the reason for withdrawal. Responding is voluntary and we will not put pressure on the parents to make them respond.

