### **3.3 Randomization and blinding**

Randomization will be performed in blocks of 12 children, to assure equal allocation to the two study groups over the year. A computer generated randomization list with 200 consecutive 'order numbers' (1, 2, 3, ..., 200) will be produced before study start by a staff member not involved in the practical study work. When meeting for the pre-visit each participant will be assigned a unique ID number (in the format D218xxx). At the end of the baseline visit the prospective participant is assigned to one of the two intervention groups by the investigator querying the randomization sequence, thus linking participant ID to a number in the randomization sequence and consequently randomly to one of the intervention groups. For example, if the child with ID number D218004 is the second child to finish his baseline visit, he will be assigned to 'order number' 2 on the randomization list, which, according to the list corresponds to e.g. poultry group. This procedure assures optimal data handling and quality, as all test and papers related to the child can be assigned the unique study ID number already from the pre-visit, while at the same time assuring that group allocation is not performed until after the baseline measurements. This procedure ensures blinding of both participants and investigators until the baseline measurements have been completed. Due to the taste and nature of the intervention foods, blinding of study staff and participants is not possible through the entire study.

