| Information meeting at NEXS
(1 hour) | 
 
• An understandable presentation of the context and purpose of the study
 
• Explanation of the study procedures and measurements.
 
• Any foreseeable risks, side effects, complications and inconveniences
 
• Unpredictable risks
 
• The right for time to reflection
 
• Volunteering
 
• Confidentiality
 
• The right to decline information on the study results
 
• That all data collected during the study will be used in the event of a participant chooses to withdraw from the study
 
• Description of the study products/food
 
• Review of the pamphlet "Before you decide" published by DNVK August 2014
 
• Questions from the parents
 
• Explanation of informed consent and withdrawal
 
 |
| Pre-visit at NEXS
(1 hour)           | 
 
• Informed consent
 
• Inclusion/exclusion criteria
 
• Instructions on 4-day dietary recording
 
• Instructions on accelerometer measurements
 
• Cognitive pre-testing
 
                                                                                                                                                                                                                                                                                                                                                                                                                                                                                                                                                                                              |

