## **5. STATISTICAL CONSIDERATIONS**

### **5.1 Statistical power**

The primary outcomes of the study will be diastolic blood pressure and plasma triacylglycerol. Power calculations were performed using data from our previously conducted OPUS School Meal Study (23). With 150 completing children we will have 80% power to detect a difference of less than 0.5 SD of the outcomes i.e. 2.7 mmHg in diastolic blood pressure and of 0.13 mmol/L in triacylglycerol between the two intervention groups, respectively. This would correspond to approximately 4% reduction in blood pressure and 20% reduction in plasma triacylglycerol among this age group, which is considered relevant and obtainable.

The cognitive measurements will be secondary and exploratory outcomes, and therefore not subject to power calculation. However, in the OPUS School Meal Study we previously found that school meals rich in fish improved school performance and reading comprehension in Danish 8-11 year-olds (52). Although the sample size was about 4 times larger in that study, the fish group of FiSK Junior will get 5-10 times more n-3 LCPUFA than in the school meal study, and therefore we expect FiSK Junior to have a sufficient sample size for the cognitive outcomes as well.

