## **6. COMPLIANCE MEASUREMENT**

The content of n-3 LCPUFA in erythrocytes will be used as biomarker of compliance, reflecting intakes over the last 3-4 months. Also, during the 12 weeks intervention period parents will be asked to register the child's intake of study foods as another measure of compliance.

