### 9.2 Informed consent

The parents or custody holders of the child will be informed orally and in writing about the study, and have to be legally able to give written consent for the child's participation. Parents/ custody holders can withdraw their consent for participation at any time without giving explanations and without any consequences for them or the child. Parents will be informed that data, that was collected before withdrawal, may be used by the investigators in the data analysis of the study. If they do not wish this use of their data, they must tell us to delete their data from the data set. The informed consent gives all relevant authorities that regulate the study, such as the Danish National Committee on Biomedical Research Ethics, consent to see the data of the participants.

We will not perform any study activities until both parents or all custody holders have given written consent based on oral and written information on:

- The study and its activities and procedures
- Their right to withdraw from the study at any time without giving explanations and without consequences
- The procedures for collection and storage of the personal and biomedical data
- That the personal and biomedical data will be processed anonymously

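### Section 3.5.3 allows exclusion for non-compliance after open allocation without saying the child is still measured, which could bias both primary comparisons

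*Protocol*

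**What the plan says.** Section 3.5.3 lists three grounds for exclusion: medical reasons, ethical reasons such as a child who does not want to go on, and non-compliance. The third reads: "Finally, a participant can be excluded if non-compliance with the procedures described in the information material is clearly demonstrated". No threshold is given, and for this ground nobody is named as deciding. The only stated follow-through is "Reasons for exclusion will be recorded and parents will be informed about the decision".

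Section 3.3 fixes the timing: "At the end of the baseline visit the prospective participant is assigned to one of the two intervention groups". After that point, "blinding of study staff and participants is not possible through the entire study".

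Information on compliance builds up during the intervention. Families collect food every one to two weeks (Table 1), intake of study products is registered weekly (section 4.5), and section 6 adds that "parents will be asked to register the child's intake of study foods as another measure of compliance". Section 6 also names n-3 LCPUFA in erythrocytes as the compliance biomarker.

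Two places deal with the data of children who leave. The list for the information meeting in Table 1 includes "That all data collected during the study will be used in the event of a participant chooses to withdraw from the study". Section 9.2 says "Parents will be informed that data, that was collected before withdrawal, may be used by the investigators in the data analysis of the study". Both concern withdrawal by the family.

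The primary outcomes are diastolic blood pressure and plasma triacylglycerol (section 2). Both are to be compared by analysis of covariance with the baseline value as covariate (section 5.2).

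**The concern.** Compliance with the diet can only be observed after the child has been allocated. If a child leaves because of it, the decision follows randomisation and is made in a trial where the arm is known. If the share of children removed differs between arms, and those removed differ in outcome from those kept, the remaining groups are no longer comparable by design.

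The protocol gives some reason to expect unequal pressure. Children enter eating fatty fish at most once a week (section 3.5.1) and are then asked for 300 g a week over two dinners and three lunches (section 3.2). The quoted median fish intake of Danish 4-9-year-olds is about 70 g a week (section 1.2.1), against almost 600 g a week of meat and meat products (section 7.1). The same 300 g is thus about 300/70 = 4.3 times the habitual fish intake, but about 300/600 = half the habitual meat intake.

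This matters at protocol level because it is a rule of conduct. A statistical analysis plan can define who is analysed and how missing values are handled. It cannot supply a blood pressure reading or a blood sample that was never taken.

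**Working it through.** **1. The protocol's own figure.** Section 5.1 says "With 150 completing children we will have 80% power" for a difference below 0.5 SD, namely 2.7 mmHg and 0.13 mmol/L. With 75 per arm and two-sided alpha 0.05 (assumed; the protocol states none), the detectable difference is

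(1.960 + 0.842) × √(2/75) = 0.457 SD,

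or 0.460 SD by the t-test. The statement is reproduced. The implied SDs are 2.7/0.457 = 5.9 mmHg and 0.13/0.457 = 0.28 mmol/L.

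**2. Bias from selective exclusion.** Let a share p of an arm be excluded, and let the excluded children lie δ SD above the mean of their whole arm. The mean of those retained then shifts by −pδ/(1 − p). The bias in fish minus poultry is

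−δ × [pF/(1 − pF) − pP/(1 − pP)].

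The protocol gives no exclusion rate and no δ, so all the rates and gaps below are assumptions:

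- 10% fish, 2% poultry: 0.1111 − 0.0204 = 0.0907.
- 20% fish, 5% poultry: 0.2500 − 0.0526 = 0.1974.

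| Excluded, fish / poultry | δ (SD) | Bias, absolute (SD) | mmHg | mmol/L |
|---|---|---|---|---|
| 10% / 2% | 0.3 | 0.027 | 0.16 | 0.008 |
| 10% / 2% | 0.5 | 0.045 | 0.27 | 0.013 |
| 20% / 5% | 0.3 | 0.059 | 0.35 | 0.017 |
| 20% / 5% | 0.5 | 0.099 | 0.58 | 0.028 |

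Against 2.7 mmHg this is 0.16/2.7 = 6% to 0.58/2.7 = 22%.

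**3. Sensitivity to how the gap is defined.** If the gap is measured between excluded and retained children, the bias is (pF − pP) × gap. A difference in exclusion of 5 to 15 percentage points with a gap of 0.25 to 0.5 SD gives 0.013 to 0.075 SD (0.07 to 0.44 mmHg; 0.004 to 0.021 mmol/L). With standard error √(2/75) = 0.163 SD, the type I error is then 5.1% to 7.5% instead of 5%. A deliberately extreme case, 15 points and a gap of 1 SD, gives 0.15 SD (0.89 mmHg; 0.043 mmol/L) and a type I error of 15%.

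**4. The null case.** With equal exclusion rates and equal gaps in both arms, the bias is zero under either formula.

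**5. Do other passages close the gap?** Table 1 and section 9.2 apply when the family withdraws, not when the child is excluded, and section 9.2 covers only data collected before withdrawal. Neither provides for an endpoint measurement. Covariance analysis of a child with a baseline value only needs an endpoint value that does not exist.

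**The case against.** The strongest reply is that the rule is permissive, sets a high bar and requires the reason to be recorded, so it may seldom be used. The design also works against unequal compliance: children must like both oily fish and chicken and accept either allocation (section 3.5.1), and both arms get free food for family dinners and matched recipe booklets (section 3.2). This stands as a limit on the likely size. It does not remove the open-ended ground or provide the missing endpoint visit.

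Several stronger readings are tempting and are not supported:

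- **That the rule does bias the results, or does so in favour of fish.** No passage says that exclusions will differ by arm or how excluded children would differ in outcome. The dietary argument is indirect: the intake figures are for 4-9-year-olds in general, and no habitual poultry intake is given.
- **That unblinded staff decide on food intake.** The sentence names no decision-maker and covers procedures in general, which could include fasting or recording. Dietary non-compliance judged by people who know the arm is a fair inference from section 3.3, but it is not stated.
- **That excluded children are dropped from the analysis.** Section 3.5.3 does not say so, and the analysis population may be settled in the statistical analysis plan.
- **That a power statement based on completers is itself a defect.** Section 3.6 raises 150 to 200 for drop-out and failed blood sampling. It does not say whether exclusions count within the drop-out figure, so treating them as an extra loss would be an assumption.

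The upper scenario is also severe: 20% excluded from the fish arm for this reason alone equals the top of the drop-out range planned in section 3.6. Finally, if δ is meant conditional on baseline and the implied 5.9 mmHg is an unadjusted SD, the mmHg figures are somewhat too high.

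**Conclusion.** The point holds as a risk created by the wording of section 3.5.3. The protocol allows exclusion for non-compliance after an allocation that everyone knows, sets no criterion, and does not say that the child is still measured. This could bias both primary comparisons, and the lost endpoint values could not be restored later.

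The size cannot be determined from the protocol. Under the assumed rates and gaps it is about 0.03 to 0.10 SD, which is modest against the design difference. Larger values need extreme assumptions, and equal rates and gaps give none. The case for a change therefore rests on data that cannot be recovered and on a very cheap remedy, rather than on a large expected bias. Severity: should-fix.

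**What to change.** In section 3.5.3, state that:

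- after randomisation, non-compliance is not a ground for ending follow-up;
- every randomised child whose family agrees is invited to the endpoint visit, whatever amount of study food was eaten, and stays in the allocated group for the primary analysis;
- compliance, from the intake records and erythrocyte n-3 LCPUFA in section 6, is used only in a secondary analysis.

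Leave the medical ground, the ground for a child who does not want to continue, and the parents' right to withdraw as they are. Losses by those routes could also differ by arm, so the change reduces the risk without removing it.

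The cost is a few sentences of wording, a few extra endpoint visits, and an estimate slightly diluted by children who ate little of the study food.

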## **3. METHODS**

### **3.1 Study design**

The study has a block-randomized controlled 12-week parallel design (**Figure 1**). It will include two groups of 100 children each; one group that receives fatty fish and one group that receives poultry.

The study participants will be 8-9 year-old healthy Danish children who will be enrolled from summer 2016 to April 2017. Apart from an information meeting the study consists of a pre-visit, a baseline visit and an endpoint visit which will be held at Department of Nutrition, Exercise and Sports (NEXS), [name].

[figure not shown]

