### **3.6 Recruitment of study participants**

A total of 150 children completing the study are needed. From our previous studies in children we expect a drop-out of up to 15-20%, and expect unsuccessful blood sampling in an additional 10% of the children at either baseline or endpoint. Therefore, a total of 200 participants will be recruited.

Boys and girls of the relevant age will be identified through the Danish Civil Registration System (CPR registry) and recruited via postal invitation letter to the parents (Appendix 2). Participants will mainly be recruited from the Capital Region of Denmark, but if necessary also from other parts of Zealand. Participants may also be recruited through advertisements in Danish newspapers, shared through networks and social media such as Facebook, and by notices in schools and after school clubs (Appendix 6). Parents that respond to the advertisements will receive the same information material as parents contacted through the CPR registry. The letter will contain a link to an electronic response form and the information material (Appendix 3). The brochure "The legal rights of study participants in a health science research project" [Forsøgspersonens rettigheder i et sundhedsvidenskabeligt forskningsprojekt], published by the Danish Committee on Biomedical Research Ethics system in August 2014, will be included in the information material.

Parents are asked to carefully read the material, if they wish together with a family member or a friend, and to explain the content to their child. Parents who return the response form will be called by telephone by the project staff. Here the participants will be pre-screened according to the inclusion and exclusion criteria. If they are still interested in participating, they will be invited to an information meeting where the study will be explained orally to parents and child by a project staff member who has been specifically trained for this task. Parents will be informed that they can bring an assessor (e.g. a family member or a friend) to the information meeting, if they wish so. If the participants do not fulfil the criteria for participation they will be informed hereof and will not be contacted or bothered further. Only one eligible child from each household can be included as a study participant, since for practical reasons individual randomization within a household is not possible.

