### **4.2 Cardiovascular function**

#### **4.2.1 Blood pressure and heart rate**

Blood pressure and heart rate will be measured three times by an automated device with the child lying down after 10 minutes rest. The appropriate cuff size for the child's arm circumference will be used. This procedure will be repeated up to four times during the five hour baseline and endpoint visits to account for potential variation in blood pressure during the visits and thereby obtain the most accurate measure of the primary outcome.

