### **5.2 Statistical analysis**

The effect of the intervention on the outcomes will be evaluated using analysis of covariance including baseline outcome values as covariate. Outcomes will also be analyzed with gender and genotype as potential effect modifiers.

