**In conclusion, the study foods are therefore considered safe for the participants.**

## 7.2 Safety of study procedures

Blood samples will be taken by experienced laboratory technicians who are used to taking blood samples in children, and the only expected risk in relation to blood sampling is the risk of a mild pain and potentially a small bruise at the site of the prick, which will disappear within a few days. The volume of the blood sample is small (40 ml per sample) and the two blood samples are taken three months apart. To reduce the discomfort of blood sampling we will provide local anesthetic patches (EMLA) to the parents, containing lidocaine and prilocain, to put on both forearms at home before the blood sampling. The patches are sold over-the-counter in Danish pharmacies.

Bio impedance is non-invasive and has not been reported to give untowards events. A very small electric current is sent through the body, however it is lower than the threshold of perception and unlikely to stimulate electrically excitable tissues such as heart and cardiac muscle. The method has been approved by the US Food and Drug Administration.

The cold pressor test generally causes some cold-related pain, but this risk is balanced by the participants' control over the process (i.e., their ability to withdraw their hand if it becomes too uncomfortable) and the fact that the cold-related pain mounts fairly slowly so that it can be terminated before it becomes too uncomfortable (60). As a further means of minimizing risk, the following guidelines published by Von Baeyer and colleagues (2005) will be followed: Children with a history of cardiovascular disorder, fainting or seizures, frostbite, open cut, sore or fracture of hand to be immersed, and any history of Reynaud's phenomenon (hands get white, then blue, on

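### Section 3.5.3 does not separate stopping the study foods from leaving the study, so children who leave early have no observed value for either primary outcome

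*Protocol*

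**What the plan says.** On families who want to stop, Protocol section 3.5.3 says: "Parents will be informed that they can withdraw their child from participation at any time without giving a reason". Staff then ask for the reason, and answering is optional. No other step follows. The same section gives staff a separate, optional power: "a participant can be excluded if non-compliance with the procedures described in the information material is clearly demonstrated".

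On when outcomes are measured, section 3.1 says that, after the information meeting, "the study consists of a pre-visit, a baseline visit and an endpoint visit". For blood pressure, section 4.2.1 says: "This procedure will be repeated up to four times during the five hour baseline and endpoint visits". For blood, section 7.2 says that "the two blood samples are taken three months apart". For the weeks in between, Table 1 lists only collecting, eating and registering the study foods.

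On losses, section 3.6 says: "From our previous studies in children we expect a drop-out of up to 15-20" per cent. It allows a further 10% for failed blood sampling and recruits 200 children so that 150 complete.

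On analysis, section 5.2 specifies "analysis of covariance including baseline outcome values as covariate" and names no analysis set.

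On withdrawn children's data, Table 1 has parents told that "all data collected during the study will be used in the event of a participant chooses to withdraw from the study". Section 9.2 refers to data gathered before withdrawal and lets parents have them deleted.

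**The concern.** A child can stop eating the allocated food and still have blood pressure and a fasting blood sample taken at 12 weeks. The protocol does not provide for this. A family that has had enough of the food is offered only withdrawal from participation, and nothing prompts staff to ask for the endpoint visit. With no outcome visit in between, the child is left with a baseline value alone.

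This is a rule of conduct. A statistical analysis plan can define populations and imputation, but it cannot supply measurements that were never taken.

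What is at stake is the comparability of the arms. Section 3.3 states that blinding cannot be kept up throughout the study. The foods differ and are to be eaten five times a week (section 3.2), so tiring of one of them is a plausible reason to stop that depends on the arm. If so, the children with an endpoint value are a selected part of each arm. The results are also meant to inform dietary recommendations for children (section 9.5), for which the effect in all randomised children is relevant.

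**Working it through.** **1. The protocol's own figure.** Inputs from section 5.1: 150 completing children (75 per arm), 80% power, 2.7 mmHg. The significance level is not stated; two-sided 5% is assumed.

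- Detectable difference = (1.960 + 0.842) × √(2/75) = 0.457 SD. This agrees with the stated value of less than 0.5 SD.
- Implied SD of diastolic pressure = 2.7 / 0.457 = 5.9 mmHg.

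The figure reproduces, and it counts completing children.

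**2. Children without an endpoint value.** Inputs from section 3.6.

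- 200 × 0.15 = 30 and 200 × 0.20 = 40 children, leaving 170 to 160 with an endpoint diastolic pressure.
- Power at 0.457 SD is then 0.85 to 0.82, so power is not the problem.
- For triacylglycerol, the further 10% leaves 150 to 140 pairs if it is taken of all 200 (170 − 20, 160 − 20), or 153 to 144 if taken of those remaining (170 × 0.9, 160 × 0.9). Failed blood samples are a separate loss that this point does not address.

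**3. The sections side by side.** Section 3.5.3 offers withdrawal and a voluntary question. Sections 3.1, 4.2.1 and 7.2 place both primary outcomes at baseline and endpoint only. Section 9.2 foresees no data after withdrawal. Together, a withdrawn child has no observed primary outcome.

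**4. Possible size, for illustration only.** Every input below except 2.7 mmHg, the 15-20% and the implied SD is assumed.

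- *Dilution.* Suppose the effect is 2.7 mmHg in children who complete and zero in all who leave. The effect in all randomised children is then 2.7 × 0.85 = 2.30 or 2.7 × 0.80 = 2.16 mmHg. The completers' figure is larger by 1/0.85 − 1 = 18% or 1/0.80 − 1 = 25%.
- *Selection.* Bias = (drop-out in fish arm − drop-out in poultry arm) × gap between leavers and completers × SD. With 20% v 15% and a gap of 0.25 SD: 0.05 × 0.25 × 5.9 = 0.07 mmHg. With 30% v 10% and a gap of 0.5 SD: 0.20 × 0.5 × 5.9 = 0.59 mmHg. Baseline adjustment would remove whatever part of the gap the baseline value predicts.

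**5. Power for diastolic pressure if all 200 were measured.** At 0.457 SD in every child, power is 0.90. If 15% or 20% had no effect at all, the standardised effect is 0.457 × 0.85 = 0.389 or 0.457 × 0.80 = 0.366. Power is then Φ(0.389 × √50 − 1.960) ≈ 0.79 or Φ(0.366 × √50 − 1.960) ≈ 0.74.

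**The case against.** The strongest reply is that section 3.5.3 states an ordinary right to withdraw and nothing more. A reader might infer that a family that stops the foods must leave the study. No sentence says so. Intake is registered weekly and erythrocyte n-3 fatty acids serve as a compliance marker (sections 4.5 and 6), which suggests that children with imperfect compliance are expected to stay. Exclusion for non-compliance is optional. A child who is not excluded could attend the endpoint visit. All of this stands: the protocol is silent here and does not prohibit attendance.

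A reader might also infer that the primary analysis is restricted to completers. Section 5.2 names no analysis set, the 150 completing children are a sample-size figure, and the analysis set and missing-data method may be in an analysis plan that is not shown.

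Nor does Table 1's statement on withdrawn children's data conflict with the rest. It concerns data already collected, and baseline data satisfy it. It promises no endpoint value.

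On size, the objection also has force. The drop-out figure is an upper limit without reasons. Visits last 4-5 hours and involve fasting and a blood draw, and families who leave because of that burden would not be recovered. The 18-25% partly contrasts two different effects, that of eating the food and that of being assigned to it, and 2.7 mmHg is a detectable difference and not a forecast. Children must like both foods and accept either (section 3.5.1), and the aquarium pass is handed over at the endpoint visit (section 13). Both features should limit the loss.

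None of this supplies an endpoint value for a child whose family stops the food and is never asked to return.

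**Conclusion.** The point holds as a gap in the conduct rules. Stopping the study foods and withdrawing from the study are not separated, no endpoint visit is requested from families who stop, and a child who leaves between baseline and endpoint has no observed primary outcome. Up to 30-40 of 200 children could be affected. The recoverable part is limited to those who stop because of the foods, and that share is unknown.

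Arm-related drop-out in an open trial could bias the comparison, but neither its direction nor its size can be derived from the protocol. The 2.16-2.30 mmHg and 0.07-0.59 mmHg figures show only what the assumed inputs would imply. The sample size is not in question. This is a low-cost improvement worth making, not an error in a stated rule.

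**What to change.** In section 3.5.3 and the participant information material, state that stopping the study foods is not withdrawal from the study. Ask each such family, on a voluntary basis, whether the child will attend the endpoint visit as planned, at minimum for blood pressure and the fasting blood sample. The right to leave the study altogether stays as it is. The sentence on exclusion for non-compliance should be worded so that it does not conflict with this. Analyse these children in the group to which they were randomised; the details can go in the analysis plan.

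The cost is a paragraph in each document, submitted as a supplementary protocol if it counts as a major change under section 9.1, and some additional endpoint visits within the 200 children already planned. Some families will decline. The estimated effect may be smaller because children who stopped are included; in the extreme case worked above, power for diastolic pressure would be about 0.74-0.79. A side benefit is that these families would also be asked about adverse events, a question that section 9.4.8 places at the endpoint visit.
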